### Statistical analysis

To assess the training effects on the study outcomes, we will analyze the data according to the intention-to-treat principle [37]. When post-test data are missing, baseline scores will be considered post-test scores. We will use a two-factor (group and time) analysis of variance (ANOVA) with repeated measures. We will repeat the analysis using the actual blinding of assessment staff to participant randomisation assignment (successful or not), baseline values of age, body mass index, MMSE, number of falls within the previous year and handgrip strength as covariates. For each outcome variable we will report the level of significance corresponding to the main group (between-subjects), time (within-subjects) and interaction (group × time) effects. We will perform post hoc pre- vs. post comparisons by group only when a significant group*time effect is present. The level of significance will be set to = 0.05. We will adjust multiple comparisons for mass significance [38]. We will use the Student’s *t* test (or its non-parametric equivalent, the Mann Whitney’s *U* test) for comparing between the two groups the mean values of those secondary outcomes that will be assessed only once, i.e. three months after discharge (number of falls, Katz score and Barthel index). We will compare mortality rate at three months after discharge in the two groups with the chi square test.

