## Background

Due to Western societies populations living longer there is a demand to explore new ways to promote healthy ageing instead of merely treating the diseases of old age [1]. According to the United Nations (average for the 2005–2010 period), Spain has the sixth longest life expectancy at birth in the world [2]. Therefore, especially in Spain, it is of public health and clinical relevance to better understand the effects of regular physical activity in old people. This is not only true for non-hospitalized individuals, but also includes hospitalized older individuals.

The negative effect of hospitalisation on functional outcomes in population-based [3] and in-hospital cohort studies is well-established [4,5]. This negative effect occurs even with short (several days) hospital stays [6-8]. Ten days of bed rest result in significant losses of whole body lean tissue, lower body lean tissue and strength in healthy 67-year-olds [7]. Loss of strength with bed rest can be as great as 5% per day [9]. With such significant losses of strength it is not surprising that even short hospital stays result in a decrease in functional capacity, including the ability to cope with activities of daily living (ADLs). In fact 30–50% of seniors admitted for a short hospital stay show a decrease in functional capacity at discharge [10-14]. These decreases in functional capacity are associated with an increased risk of mortality. For example, individuals showing the least decrease in functional capacity with a hospital stay have a mortality rate of 10.7% three months after discharge compared to 36.7% in individuals showing the greatest decrease in functional capacity [15].

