### Sample size and statistical power

The required sample size was determined for one of the primary outcome variables, i.e. the SPPB. We believe that a clinically relevant change is a ≥30% increase in the aforementioned test battery. We expect the control group to improve ~0 to 5%; thus, we can detect differences of at least ≥35% with a power >80% and a level of significance of 0.05 with two groups of 60 subjects. Assuming a maximum loss of follow-up of 20%, we will recruit a total of 150 patients.

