#### *Assessment after discharge*

We will perform a follow-up phone interview with participants (or their relatives/caregivers in case of death) three months after discharge, to determine mortality rate after three months and number of falls within three months after discharge, and also to subjectively assess the ability to cope with ADLs using the Katz ADL score [24] and the Barthel ADL index [25].

The Katz ADL scale includes six items (eating, transferring from bed to chair, walking, using the toilet, bathing, and dressing) each of which is scored with 0 (= unable to perform the activity without complete help), 0.5 or 1.0 (= able to perform the activity with little help or without any help, respectively) [24]. A sum-score (ranging from 0 to 6) is given for each patient. The Barthel index is an instrument widely used to measure the capacity of a person for the execution of ten basic activities in daily life, obtaining a quantitative estimation of the subject’s level of independency [25,32]. The ten items include: eating, transferring from bed to chair, using the toilet, bathing/showering, personal hygiene (e.g., tooth brushing, shaving) dressing, walking, stair climbing, and bowel and bladder control. Each individual item is scored with 0 (i.e. unable to perform without complete help or fecal/urine incontinence), 5 (i.e. able to perform the activity with little help or only accidental fecal/urine incontinence) or 10 (i.e. able to perform without any help or total fecal/urine continency). The sum-score ranges from 0 (*totally dependent*) to 100 (*totally independent*).

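### Replacing every missing discharge score with the admission score records untested and deceased patients as unchanged, which dilutes the training effect or, when loss differs by arm, biases it

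*Protocol article*

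**What the plan says.** The Statistical analysis section of the protocol article commits to intention to treat ("we will analyze the data according to the intention-to-treat principle") and then fixes how gaps are filled: "When post-test data are missing, baseline scores will be considered post-test scores". No reason for missingness is treated differently, and no other analysis of missing data is named. The filled data go into the main test of the discharge outcomes: "We will use a two-factor (group and time) analysis of variance (ANOVA) with repeated measures".

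Three other sections bear on the rule:

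- **Sample size and statistical power** plans for loss: "Assuming a maximum loss of follow-up of 20%, we will recruit a total of 150 patients". It takes a rise of at least 30% in SPPB as clinically relevant, expects controls to improve by about 0 to 5%, and powers the trial for a difference of at least 35% with 60 patients per group.
- **Background** reports that "30–50% of seniors admitted for a short hospital stay show a decrease in functional capacity at discharge".
- **Primary outcome (functional capacity) measures** gives a score of 0 on the chair-stand or 4-metre walk component of the SPPB to a patient who cannot complete it. It gives no value for a 10-metre walk that cannot be completed.

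**The concern.** Carrying the admission score forward assumes that a patient with no discharge test did not change. The article's own premises make that a poor guess in either direction. It is too favourable for a patient who died or was too ill to be tested, since decline in hospital is said to be common. It is too unfavourable for a trained patient who simply was not tested, since the trial looks for a large gain.

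The 10-metre walk has a further gap. If a patient who can no longer walk that distance is treated as having a missing time, the rule enters the admission time, and loss of walking ability is recorded as stability on a primary measure.

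The size of the primary effect is at stake, and its direction may be too if loss differs between the arms.

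**Working it through.** Points below are percentage points of change in SPPB, the scale used in the sample-size section, not points on the 0–12 score.

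**1. The plan's own figure.** Two groups of 60 with 20% loss: 120 / (1 − 0.20) = 150. This reproduces the stated total. At that loss, 0.20 × 150 = 30 patients would carry a filled-in zero change.

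**2. The SD, which is not stated.** Solving back from 60 per group, 80% power and two-sided 0.05 (sidedness is assumed) for a 35-point difference:

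SD = 35 × √(60/2) / (1.960 + 0.842) ≈ 68.4 points.

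This SD is an assumption and is used only for the power figures.

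**3. Data missing at random.** Let a share m_T of the training arm and m_C of the control arm be missing. With true mean changes d_T and d_C, the filled difference is (1 − m_T)·d_T − (1 − m_C)·d_C. Take d_T = 35, d_C = 0 and 75 per arm. The variance of the filled change in an arm is (1 − m)·SD² + m(1 − m)·d².

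| Missing, control / training | Filled difference | Power |
|---|---|---|
| 0% / 0% | 35 | 88% |
| 10% / 10% | 0.9 × 35 = 31.5 | 84% |
| 20% / 20% | 0.8 × 35 = 28 | 79% |
| 10% / 30% | 0.7 × 35 = 24.5 | 67% |

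For the 20% / 20% row the variances are 0.8 × 68.4² ≈ 3746 in control and 3746 + 0.16 × 35² = 3942 in training. The standard error is √((3746 + 3942)/75) ≈ 10.1, and 28/10.1 − 1.96 ≈ 0.81, which gives 79%.

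For comparison, 60 observed patients per arm with no filling give a standard error of 68.4 × √(2/60) ≈ 12.5 and 80% power. At the planned maximum loss the rule therefore costs about one point of power against the design. The larger harm is to the estimate, which is 20% too small.

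**4. Missing patients who truly declined.** Suppose the missing patients fell by X and the observed patients did not change in either arm. The filled difference is 0, while the true difference (training minus control) is −X·(m_T − m_C). The arm with more loss is credited with X × (difference in loss):

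- X = 30, 20% versus 10% missing: 30 × 0.10 = 3 points.
- X = 50, same loss: 5 points.
- X = 30, 30% versus 10% missing: 30 × 0.20 = 6 points.

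Either arm can be the one favoured.

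**5. Equal loss and equal decline.** With 20% missing in each arm and a 30% fall among them, the true mean changes are 0.8 × 35 − 0.2 × 30 = 22 and 0 − 0.2 × 30 = −6, a difference of 28. The filled means are 28 and 0, also a difference of 28. The comparison between arms is unbiased.

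**6. Type I error.** In a simulation of 20,000 trials with 75 per arm, SD 68.4, 20% missing at random in each arm and no true effect, a t test on change rejected in 4.8% of trials. This test is equivalent to the group-by-time test with two time points. With a true 35-point effect, the mean standard error was 10.1, the empirical standard deviation of the difference was 10.1, and power was 79%.

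**The case against.** Much can be said for the plan:

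- **SPPB scoring protects tested patients.** A patient who lost function and was tested has a real, low score. The defect is confined to untested patients and possibly to 10-metre times. This stands.
- **In-hospital death may be uncommon.** The exclusion criteria remove terminal illness and unstable disease. The 20% is a stated maximum, and part of it may fall at the three-month interview rather than at discharge. This stands, and it makes the 20% row a worst planned case.
- **The rule is often conservative.** Under equal random loss it shrinks the effect and creates no false positives. This is true, but it does not help when loss differs by arm.

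A reader might infer four stronger points that the document does not support:

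- **That standard errors are too small because filled values count as observed.** Step 6 shows that the standard error is right for the filled quantity.
- **That a gain is always understated.** Dilution requires the missing patients to have changed as the observed ones did. Step 5 shows that it disappears when they declined equally in both arms.
- **That the rule breaks down for Katz and Barthel, leaving a comparison of survivors only.** The article handles "those secondary outcomes that will be assessed only once, i.e. three months after discharge (number of falls, Katz score and Barthel index") separately and never says that the baseline rule applies to them. How deaths enter these secondary scales is detail that an article may leave to a fuller document. A figure for survivor bias would need invented death rates by arm.
- **That deaths in hospital go uncounted.** The article says "We will compare mortality rate at three months after discharge in the two groups with the chi square test", but nothing in it excludes deaths before discharge.

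**Conclusion.** The point holds for the two discharge measures of functional capacity. The plan fixes a single rule that enters zero change for any patient without a discharge score, whatever the reason, and this sits badly with its own statements about decline and expected gain.

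Its size depends on why data are missing. Under random loss at the stated maximum, a 35-point difference is reported as 28, with power about 79% if the SD is about 68 and 75 are enrolled per arm. If the missing patients declined, each 10-point gap in loss between the arms is worth 3 points at an assumed 30% decline and 5 at 50%, in favour of the arm with more loss. With equal loss and equal decline the difference between arms is unbiased.

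Loss by arm, the decline among missing patients and the SD are assumptions. The document gives only the 20% maximum and the design difference.

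**What to change.** Settle the following before the outcome data are analysed by group:

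1. For SPPB and 10-metre results that are merely missing, make a likelihood-based mixed model, or multiple imputation using baseline score, age and MMSE, the primary analysis. All three predictors are already collected at admission.
2. Give explicit worst values where the patient died in hospital or was unable to perform: SPPB 0, and the 10-metre walk analysed as speed with 0 for unable. Record the reason for every missing discharge test so that the two cases can be told apart.
3. Keep the baseline-carried-forward analysis as a sensitivity analysis.

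The cost is a little more analysis work. The primary result becomes a composite that mixes death with function, so the observed values should be shown beside it. A worst-rank analysis of Katz and Barthel that includes deaths could be added as an optional supplement, but this point does not require it.

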### Randomisation and blinding

As mentioned above, randomization will be done in a time-dependent manner (in four-week blocks) in order to avoid the confounding variable of participants in the control group seeing subjects in the treatment group performing physical activity in addition to normal hospital care. Participants will be explicitly informed and reminded not to discuss their randomisation assignment with assessment staff. The assessment staff will be blinded to participant randomisation assignment, as well as to the main study design and to what changes we expect to occur in the study outcomes in either group. Because blinding of assessment staff to participant randomisation assignment might not be actually feasible in all cases due to the time-dependent manner of randomisation, we will record blinding success and add it as a covariate in the analyses (see below). It will not be possible to conceal the group assignment from the staff involved in the training of the intervention group.

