### Covariates

Besides actual blinding success of assessment staff to participant randomisation assignment, the following covariates will be measured in all participants upon hospital admission as they could influence one or more of the study outcomes.

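### Assessor blinding success, a post-allocation variable, enters the only adjusted model described and can bias the adjusted group effect

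*Protocol article*

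**What the plan says.** The main analysis in the Statistical analysis section has no covariates: "We will use a two-factor (group and time) analysis of variance (ANOVA) with repeated measures". It is then run again: "We will repeat the analysis using the actual blinding of assessment staff to participant randomisation assignment (successful or not", alongside "baseline values of age, body mass index, MMSE, number of falls within the previous year and handgrip strength as covariates". This is the only adjusted analysis that the article describes.

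The Randomisation and blinding section makes the same commitment. It concedes that keeping assessors blind "might not be actually feasible in all cases due to the time-dependent manner of randomisation", and answers: "we will record blinding success and add it as a covariate in the analyses (see below". The same section relies on patients not to disclose their arm: "Participants will be explicitly informed and reminded not to discuss their randomisation assignment with assessment staff".

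The Covariates section separates this variable from the others: "Besides actual blinding success of assessment staff to participant randomisation assignment, the following covariates will be measured in all participants upon hospital admission". Blinding success is therefore not one of the admission measurements. No other section withdraws it or limits it to a descriptive report.

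**The concern.** Covariate adjustment in a randomised trial is safe when the covariate cannot be influenced by allocation. The five baseline covariates meet that condition. Blinding success does not, because an assessor cannot learn an assignment before it exists.

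Two routes matter:

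- **Arm.** Patients know whether they are training and may say so. The article itself ties blinding failure to the allocation scheme. Training patients have up to three supervised sessions a day, and controls have none of these, so there is more to disclose in one arm.
- **Outcome.** The SPPB and the 10-metre walk are observed performance tests. An assessor who sees marked improvement at discharge may guess that the patient trained.

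If both routes operate, blinding success is a common effect of arm and outcome. Conditioning on it induces an association between arm and outcome that is not the treatment effect.

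Because the variable is bundled with legitimate baseline covariates, a disagreement between the adjusted and unadjusted results could not be read. It might reflect baseline imbalance, removal of observer bias, or distortion from the post-allocation term. The covariate is also offered as the answer to an admitted weakness in blinding, so that weakness may look handled when it is not.

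**Working it through.** **Inputs from the article.** Two groups of 60, significance level 0.05, power above 80%, 20% loss, 150 recruited (Sample size and statistical power). No SD, unblinding rate or link between unblinding and outcome is given.

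**The plan's own figure.** 2 × 60 = 120, and 120 / (1 − 0.20) = 150, as stated. The power claim cannot be checked without an SD. Taking the test as two-sided (an assumption), 60 per arm gives 80% power at a standardised difference of (1.960 + 0.842) × √(2/60) = 0.511. This sets the scale for the trial-sized runs below.

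**Model (assumed).** Outcome y = effect × arm + N(0,1). Log-odds of unblinding = a + b × arm + c × y. The outcome is regressed on arm and the unblinding indicator. It is a single post-test score, not the full group × time model.

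**Large-sample results.** True effect 0.50 SD, a = −1.5, 1,000,000 simulated patients, no observer bias:

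| b | c (per SD of outcome) | Unblinded, control vs training | Adjusted effect |
|---|---|---|---|
| 2.5 | 0 | 18% vs 73% | 0.50 |
| 1.5 | 0.1 | not tabulated | 0.47 |
| 1.5 | 0.2 | not tabulated | 0.43 |
| 1.5 | 0.5 | 19% vs 56% | 0.33 |
| 1.5 | 1.0 | 22% vs 60% | 0.18 |

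The least-squares identity explains the pattern: adjusted effect = unadjusted effect − g × (difference in unblinding proportions), where g is the fitted coefficient of unblinding. For c = 0.5 the implied g is (0.50 − 0.33) / (0.56 − 0.19) = 0.46. For c = 1.0 it is (0.50 − 0.18) / (0.60 − 0.22) = 0.84. If g is zero there is no bias.

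**Precision when c = 0.** At 18.2% versus 73.1% the mean proportion is 0.457. The squared correlation with arm is (0.549² / 4) / (0.457 × 0.543) = 0.303, so the variance inflation is 1 / (1 − 0.303) = 1.43.

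**At 60 per arm** (8,000 runs per setting):

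- b = 1.5, c = 1, true effect 0 (30% vs 60% unblinded): the mean estimate moves from 0.00 to −0.25 on adjustment, and type I error from 5% to 29%.
- Same b and c, true effect 0.511 (30% vs 70%): 0.52 becomes 0.18, and power falls from 80% to 16%.
- b = 1, c = 0.5, true effect 0.511 (28% vs 56%): 0.51 becomes 0.38, and power falls from 80% to 51%.
- c = 1, no dependence on arm given outcome, true effect 0.511: 0.51 becomes 0.42.
- b = 1.5, c = 0, true effect 0.511 (27% vs 62%): 0.51 stays 0.51, and power goes from 79% to 74%.

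**When unblinding inflates the score by 0.3 SD:**

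- Both arms inflated, c = 0, true effect 0 (27% vs 62%): the unadjusted estimate is about 0.3 × (0.62 − 0.27) = 0.11, and the adjusted estimate is 0.00.
- Training arm only inflated, c = 0, true effect 0: unadjusted 0.3 × 0.62 = 0.19, adjusted 0.13.
- Both arms inflated, true effect 0.50, a = −1.5, b = 1.5: at c = 0, unadjusted 0.60 and adjusted 0.50. At c = 0.2, 0.60 and 0.43. At c = 0.5, 0.61 and 0.33.

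**The case against.** The best defence is that the covariate was chosen to deal with observer bias, and that it can do so. If unblinding depends on arm alone and inflates scores equally in both arms, adjustment recovers the true effect. With weak outcome dependence (c = 0.2) and that inflation, the adjusted estimate misses the truth by 0.07 and the unadjusted by about 0.10. So a reader might infer that the adjusted effect is certainly biased, or that the covariate can never correct assessment bias. Neither follows from the documents.

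The outcome route is plausible but not documented. The only reason the article gives for failed blinding is the time-block allocation, which works through calendar and arm. Assessors are also to be kept unaware of the main design and of the expected changes. Training is supervised by fitness specialists, and nothing says that assessors watch it. If unblinding is driven by the block, c may be close to zero and the cost is mainly precision.

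A reader might also infer that the main result is compromised, or conversely that the unadjusted result is sound. The covariate does not enter the unadjusted ANOVA, so the first does not follow. The second does not follow either, because that analysis would still carry any observer bias that exists.

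These points narrow the claim but do not remove it. The covariate can help or harm according to assumptions that the trial cannot check, and that is a poor basis for placing it in the sole adjusted model.

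**Conclusion.** The point holds as a risk, confined to the repeated, adjusted analysis. Blinding success arises after allocation, and conditioning on it can bias the group effect if it also depends on outcome. From a true 0.50 SD the adjusted effect would be about 0.43, 0.33 or 0.18 under weak, moderate or strong dependence. It would stay at 0.50, with variance up by as much as 43% in the setting tried, under none.

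All these rates and slopes are assumptions. The direction also depends on them: the effect shrinks here because improvement is taken to raise the chance of unblinding and the training arm to be unblinded more often. Full correction of observer bias needs unblinding to be unrelated to outcome and to shift scores equally in both arms. The unadjusted ANOVA and the sample size are unaffected by this covariate. The change is worth making but is not critical.

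**What to change.** - In the Randomisation and blinding, Covariates and Statistical analysis sections, remove blinding success from the adjusted model. Keep only the covariates measured at admission: age, body mass index, MMSE, falls in the previous year and handgrip strength.
- Report blinding success by arm and by four-week block.
- If observer bias is to be explored through blinding status, do it in a separate sensitivity analysis. Label it non-randomised and open to the same post-allocation selection bias. This applies equally to using status as a covariate and to restricting to assessments recorded as blind, since both condition on the same variable.

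The cost is one deleted model term and one descriptive table. Blinding success is already to be recorded, so no new data are needed and no sample-size figure changes.

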As much as 73% and 83% of the measured hospital stay of older individuals is spent lying in bed [16,17]. During short hospital stays complete bed rest and low mobility levels are associated with negative functional outcomes [6,8]. Compared to patients with higher mobility levels, patients (mean age of ~79 years) who had complete bed rest or low mobility levels of all types (physical therapy, activity initiated by others, self initiated activity) during short hospital stays (5–8 days on average) showed greater declines in the ability to cope with ADLs, and greater risk of new institutionalization and death upon discharge and at 30 days after discharge [6,8]. The relationship between low mobility levels and negative functional outcomes is still significant after statistical multivariable adjustment for co-morbidity factors, such as severity of illness [6]. In contrast, the decline in negative outcomes with higher mobility levels follows a dose–response effect [8].

A recent meta-analysis concluded that intrahospital programs with the goal of maintaining or increasing functional capacity in hospitalized seniors result in decreased mortality rates, decreased length of hospitalization and decreased rates of discharge to nursing homes compared to discharge to home [18]. This indicates mobility and physical training are modifiable factors that have important implications for care regimes. Loss of lower body muscle mass is a strong predictor of physical performance and functional capacity in seniors [19], indicating physical training programs should emphasize the lower body musculature. Therefore, it is important to determine if increased mobility and physical training, especially of the lower body, have an effect upon functional outcomes during short hospital stays in older individuals.

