## Methods/Design

### Study design

The present study is a randomised controlled trial (RCT) (ClinicalTrials.gov ID: NCT01374893) and is designed to be compliant with the recommendations of the Consolidated Standards of Reporting Trials (CONSORT) statement [23]. The study flow diagram is shown in Figure 1. After signing an informed consent form subjects will be randomly assigned (as explained below) to either the intervention or control group. The intervention group will perform the multi-session per day training program while the control group will receive normal hospital care. Due to the possible effect of subjects in the control group seeing subjects in the intervention group performing physical activity in addition to normal hospital care, randomization will take place in a time dependent manner. Patients admitted during four-week blocks of time will all be assigned to either the treatment or control group, with a one week period between four-week periods. The participants will be followed for the length of their hospital stay, and also with a follow-up phone interview three months after discharge to determine mortality rate at three months, number of falls since discharge, and to subjectively assess the ability to cope with ADLs using the Katz ADL score [24] and the Barthel ADL index [25].

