### Demographics

A standard questionnaire including name, residence, age, reason for hospitalisation, medical history, current dosage of medications being taken and history of falls in the last year will be administered by trained investigators.

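### Reason for hospitalisation is collected but left out of the adjusted model, although allocating about 10–11 calendar blocks may by chance leave admission diagnoses uneven between the arms

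*Protocol article*

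**What the plan says.** In the protocol article, Statistical analysis comes in two steps. The first has no covariates: "We will use a two-factor (group and time) analysis of variance (ANOVA) with repeated measures". The second repeats it with whether assessor blinding succeeded and "baseline values of age, body mass index, MMSE, number of falls within the previous year and handgrip strength as covariates". The Covariates section gives the reason for its choices: "the following covariates will be measured in all participants upon hospital admission as they could influence one or more of the study outcomes". The subsections that follow cover body mass index, previous falls, grip strength and cognition.

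The Demographics questionnaire records "reason for hospitalisation, medical history, current dosage of medications being taken and history of falls in the last year". Of these four items, only the fall history reaches the model.

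On allocation, Study design says: "Patients admitted during four-week blocks of time will all be assigned to either the treatment or control group". Successive blocks are separated by a gap of one week. The study runs from June 2012 to June 2013. The article does not say whether the order of blocks is random or alternating.

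The Background reports that a cited relation between low mobility and poor outcome remained after "statistical multivariable adjustment for co-morbidity factors, such as severity of illness".

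**The concern.** The covariate list is explicit and closed, so this is a choice fixed in the text and not a detail left to an analysis plan. It was chosen for influence on outcome, yet it has no term for admission diagnosis or illness severity.

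Eligibility is not limited to particular diagnoses, and the outcomes include FEV1, SpO2 and length of stay. A respiratory admission and a non-respiratory one would not be expected to change by the same amount before discharge. That is a clinical premise, not a statement in the article.

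Two things are at stake. First, case mix over the calendar is balanced over about five blocks per arm, not 75 independent patients, so a chance gap in diagnoses can be larger than usual. Part of such a gap would be read as a training effect, or would hide one. Second, leaving out a predictor of the admission-to-discharge change costs precision even when the arms are balanced. If the term is not pre-specified, adding it after an imbalance is seen would be post hoc.

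**Working it through.** **Inputs from the article.** 60 per arm and 20% loss; four-week blocks with one-week gaps; June 2012 to June 2013.

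**The plan's own figure.** 2 × 60 / (1 − 0.20) = 150, which reproduces the stated total and gives 75 recruited per arm.

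**Number of blocks.** The cycle is 5 weeks and the last gap is not needed. Over 52 weeks, (52 + 1)/5 = 10.6; over 56 weeks, (56 + 1)/5 = 11.4. So there are 10–11 complete blocks, about 5–6 per arm.

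**Assumed, because the article gives no figures.** One diagnosis group (say respiratory) makes up 35% of admissions. Its share varies between blocks with an SD of 11 points, with 5 blocks per arm.

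**Chance gap in that share between arms.**
- Patient sampling: √(2 × 0.35 × 0.65 / 75) = 0.078. This is present under patient-level randomisation too.
- Blocks in random order: 0.11 × √(2/5) = 0.070.
- Combined: √(0.078² + 0.070²) ≈ 0.104.
- Gap above 10 points: z = 0.10/0.104 ≈ 0.96, about 34% of trials. Sampling alone gives z = 0.10/0.078 = 1.28, about 20%. Blocks account only for the rise from 1 in 5 to 1 in 3.
- Gap above 20 points: z = 0.20/0.104 = 1.92, about 5–6% of trials.

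**Range for the block component.** A simulation with 10–11 blocks and an assumed seasonal swing of ±5 to ±20 points around a 30% share gave:

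| Block order | Between-arm difference in expected share | Type I error of the unadjusted test |
|---|---|---|
| Random | SD 2–9 points | 5.0–6.7% |
| Strictly alternating | 0.1–0.4 points (10 blocks), 0.7–2.9 points (11 blocks) | 5.0–5.2% |

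The average difference is about zero in both cases. The error rates assume a diagnosis effect of 0.3–0.8 SD and 120 evaluable patients. They reflect this calendar component only.

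**Shift in the treatment comparison.** Shift = gap × extra gain in the diagnosis group. With assumed extra gains and a gap of 10–20 points:
- SPPB, 1 point: 0.1–0.2 points.
- SpO2, 3 points: 0.3–0.6 points.
- FEV1, 0.2 L: 0.02–0.04 L.

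**Precision.** Share of variance removed = p(1−p)d² / (1 + p(1−p)d²). With p = 0.35, p(1−p) = 0.2275:
- d = 0.3: 0.0205/1.0205 = 2.0%
- d = 0.5: 0.0569/1.0569 = 5.4%
- d = 0.8: 0.1456/1.1456 = 12.7%
- d = 1: 0.2275/1.2275 = 18.5%

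With p = 0.30, p(1−p) = 0.21, and d = 1 gives 0.21/1.21 = 17.4%, so the result depends little on the share.

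**The case against.** The strongest case against is that the protocol gives reasons for its covariates, and preferring another prognostic factor is a matter of judgement. The exclusions (terminal illness, recent infarction, recent fracture, unstable disease) already narrow the case mix. Admission values are in the group-by-time model, so a difference in baseline level alone does not bias the change. The calendar effect on type I error is slight, and the fix acts on a repeat analysis while the first-listed one stays unadjusted.

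Most of this stands and limits the size of the point. It does not remove it: differential recovery can still bias the change, and the precision gain does not need an imbalance.

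Three stronger readings are tempting, and the article does not support them:
- **That diagnosis mix is confounded with arm.** Nothing says case mix varies over the year. With several blocks per arm over a full year, the expected imbalance is near zero; the risk is one of chance. If blocks alternate, the seasonal part is small.
- **That the article itself shows diagnosis drives recovery of FEV1, SpO2 or function.** It does not say so; this is a plausible premise only.
- **That the Background commits the trial to adjusting for severity.** It describes how a cited cohort relation was adjusted. That relation concerned observed mobility, not allocated treatment.

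**Conclusion.** The point holds as a moderate improvement to the adjusted analysis. The article does not show that its comparison is biased. A recorded pre-allocation variable that is plausibly prognostic is missing from a closed covariate list, in a design where a small number of calendar blocks carries the balance.

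The gain is about 2–19% of residual variance for assumed diagnosis effects of 0.3–1 SD at a 35% share. The protection against bias is modest: about 0.1–0.2 points on the 0–12 SPPB scale for a 10–20 point gap, and the upper end of that gap is uncommon. All these sizes rest on assumed shares, block variation and diagnosis effects. The unstated block order alone moves the calendar component from under 3 points to as much as 9.

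A reader might infer that adjusting for diagnosis settles the consequences of block allocation. It does not: correlation within blocks and other calendar effects remain, and may matter more. With an assumed intraclass correlation of 0.01–0.05 and 12–15 patients per block, the design effect runs from 1 + 11 × 0.01 = 1.11 to 1 + 14 × 0.05 = 1.70.

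**What to change.** - Group reason for hospitalisation into a few categories fixed before the data are seen, for example respiratory, cardiac, other infection and other.
- Add it to the covariate list of the adjusted analysis together with its interaction with time. In a repeated-measures model, only that interaction adjusts the admission-to-discharge change. For length of stay, measured once, the main effect does the adjusting.
- Tabulate the categories by arm and by block.
- State whether the order of blocks is random or alternating, so that readers can judge the calendar component.

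The cost is two or three degrees of freedom and a short coding rule; no new data are needed. The change leaves the unadjusted first analysis as it is and does not replace accounting for block, which needs its own provision.
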